| DRKS ID                | As soon as the Ethics Committee has given its approval, registration in the DRKS or another primary registry is applied for in accordance with the WHO criteria.                                                                                                                                                                                                                                                                                                                                                                                                                                                                                                                                  |
| Study objective        | The study objective is to investigate the effects of an activity-based physiotherapy training programme with eye movement training compared to an activity-based physiotherapy training programme without eye movement training on dynamic balance, mobility with and without multi-task, static and dynamic balance walking speed, health-related quality of life, freezing of gait, fall-associated self-efficacy, depression and fall rate. The aim is also to explore the change in eye movements (saccade velocity, amplitude, latency, fixation duration) over the intervention period and to evaluate the feasibility of a larger randomised controlled trial using predefined parameters. |
| Primary endpoints      | 1.1 Dynamic balance measured by the Functional Gait Assessment (FGA)

1.2 Items 5, 6 and 10 of the FGA are additionally performed with eye-tracking glasses (Tobii Pro Glasses 3) for mobile measurement of eye movements (saccade velocity, amplitude, latency, fixation duration).                                                                                                                                                                                                                                                                                                                                                                                                        |

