#### **4.1.3 Randomisation and concealed allocation**

34 patients with Idiopathic Parkinson's Syndrome will be randomised into one of two groups using a 1:1 allocation ratio. For this purpose, a random number sequence generated by the randomisation software "Sealed Envelope" (<https://www.sealedenvelope.com/>) and sealed opaque envelopes are used. A stratified block randomisation (blocks of 4 and 6) with concealed allocation will be conducted by an independent researcher in the team who will not be involved in participant recruitment, instructions regarding the intervention or testing.

Stratification will be based on only one relevant predictive factor for change in dynamic mobility, namely degree of disability (H & Y stages 1 and 2; 3), due to the small sample size.

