## 5.6 Data analysis

### 5.6.1 Statistical data analysis

Statistical data analysis is performed using IBM SPSS software, version 26.0 (IBM Corporation, Armonk, NY, USA) and Tobii Pro Lab Analyser (Tobii, Danderyd, Sweden). The statistical significance level is defined by a p-value of  $<0.05$ . An attempt is made to avoid missing data by inspecting the questionnaires after completion and, in case of unanswered items, asking the study participants to complete them. The number of missing data is noted; due to the less sensitive topic of the study, it is assumed that missing variable values can be assigned to "missing completely at random" or "missing at random". An intention-to-treat analysis is performed for all cases analysed in their originally assigned group.

Descriptive statistics are used for demographic data and primary and secondary outcomes. Counted and nominal scaled data (gender, fall rate, recruitment, retention and adherence rate, number of missing data if applicable, number of adverse events) are reported as whole numbers or percentages. Ordinal scaled variables (MMSE, UPDRS, H & Y, FGA, BBS, PDQ-39, FOGQ, FES-I, BDI-II) are expressed as median (minimum, maximum or interquartile range) and metric variables (TUG, TUGman, FSST, 10MWT, eye movements: Saccade velocity, amplitude, latency, fixation duration) by mean (95% confidence interval, CI or standard deviation, SD). The data is also presented graphically (e.g. by bar charts, box plot or line graphs).

The eligibility rate (%) is the percentage of patients suitable for the study after applying the inclusion and exclusion criteria from the Parkinson's patients treated at the Reha Zentrum Münster during the study period.

The recruitment rate (%) is determined as follows:  $(N_{\text{Consent}}/N_{\text{eligible}}) \times 100$ ; where  $N_{\text{Consent}}$  is the number of participants who signed the informed consent form;  $N_{\text{eligible}}$  is the number of patients eligible for the study based on the inclusion and exclusion criteria.

The retention rate (%) is calculated as follows:  $(N_{\text{completed}}/N_{\text{Total}}) \times 100$ ; where  $N_{\text{completed}}$  is the number of participants who completed the study;  $N_{\text{Total}}$  is the total number of participants in the study.

Adherence rate (%) is determined as follows: (Actual number of exercise sessions/planned number of training sessions)\*100 (Osterberg & Blaschke, 2005).

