Eligibility, recruitment and adherence rates are calculated using the Wilson 'score' method propagated by Newcombe together with its 95% CI (Newcombe, 1998). In the case of a proportion close to 0 or 1, a Poisson approximation according to Brown is used. (Brown, Cai, & DasGupta, 2001)..

A test for statistically significant differences between the groups at baseline: for nominal data the Fisher's Exact Test is used, for ordinal data the Mann Whitney-U test and for metric data the T-test for independent samples. A preliminary inferential statistical analysis to detect trends in the effectiveness of the intervention and as a basis for sample size calculation for a randomised controlled trial with sufficient power of at least 80% (based on mean differences (SD) between groups) will be performed. For inferential statistics, metric data are first tested for normal distribution and significant data outliers using the Shapiro-Wilk test, Q-Q plots and histograms. Non-normally distributed data are transformed using suitable transformation (e.g. ln, square root), checked again and analysed non-parametrically if normal distribution is missing.

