Differences between the two groups and test times are calculated for ordinal data as follows: New variables are generated from the difference between the post-intervention and baseline data. The difference between group 1 and 2 is determined using the Mann Whitney-U test. For the ordinal variables FES-I and FOGQ, which are also collected at the follow-up call, a Kruskal Wallis test is performed across all groups and test time points. Changes in fall rate (nominal) between baseline, post-intervention and follow-up will be calculated using Chi-Square test. Metric data will be tested for homogeneity of variance (Levene test) as the basic assumption of a 2 x 2 ANOVA, with "time (baseline, post-intervention)" as the within-factor and "group (1, 2)" as the between-factor. If there is no homogeneity of variance, an alternative F-statistic (e.g. according to Welch or Brown-Forsythe) is used. If the basic assumption of sphericity is not met, corrected values are used, e.g. according to Greenhouse-Geisser or Huynh-Feldt. To calculate the differences between the groups and measurement times, a 2 x 2 ANOVA (analysis of variance) is performed, followed by pairwise comparisons (Bonferroni correction for all comparisons) between the groups at measurement times 1 and 2 if statistical significance is present. In the case of failure of the adaptive measures, non-parametric tests are used as described for ordinal scaled data.

The effect size is given by partial Eta squared and standardised effect size (Cohen's d).

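### The FGA comparison leaves out baseline FGA and the H&Y stratum, and its specified summary and test do not give the mean difference (SD) named for sizing the later trial

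*Protocol*

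**What the plan says.** The synopsis lists as a primary endpoint "Dynamic balance measured by the Functional Gait Assessment (FGA"), measured at baseline and post-intervention. Section 5.6.1 then treats the FGA as follows.

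- Summary: "Ordinal scaled variables (MMSE, UPDRS, H & Y, FGA, BBS, PDQ-39, FOGQ, FES-I, BDI-II) are expressed as median", with range or interquartile range. Means with a CI or SD are prescribed for a separate list of metric variables that does not contain the FGA.
- Analysis variable: "New variables are generated from the difference between the post-intervention and baseline data".
- Test: "The difference between group 1 and 2 is determined using the Mann Whitney-U test".
- Later use: the preliminary inferential analysis is meant to inform the following: "sample size calculation for a randomised controlled trial with sufficient power of at least 80% (based on mean differences (SD) between groups").

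Section 4.1.3 explains the randomisation: "Stratification will be based on only one relevant predictive factor for change in dynamic mobility, namely degree of disability", split into H&Y stages 1-2 and stage 3. No analysis in section 5.6.1 or the synopsis uses that stratum, and none uses a baseline value as a covariate.

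Metric outcomes (TUG, TUGman, FSST, 10MWT and the eye-movement measures) go to a 2 x 2 ANOVA of group by time. Pairwise comparisons follow "between the groups at measurement times 1 and 2 if statistical significance is present". Section 5.6.1 closes by promising partial eta squared and Cohen's d, without tying either to an outcome type.

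**The concern.** Two things do not fit together.

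First, the design collects a baseline FGA on everyone and stratifies on a factor chosen because it predicts change, but the analysis uses neither as a covariate. With N fixed at 34, adjustment is the only way to gain precision without more patients. The metric outcomes share the gap: with two time points, the group-by-time interaction is a t-test on change. The conditional pairwise tests add a group comparison at baseline, where randomisation already makes the null hypothesis true.

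Second, one stated purpose of the inferential analysis is to supply a mean difference and SD for the next trial. For the FGA, the specified outputs are a median, a rank statistic and a p-value. At stake are avoidable imprecision in the pilot estimate and no stated rule for producing the planning input for this endpoint.

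**Working it through.** **Inputs.** From the Protocol: 30 completers, 10% loss, N = 34 (section 4.1.2.3); 1:1 allocation (4.1.3); FGA range 0-30 (4.4.1.1); MDC 4 points and test-retest ICC 0.86 (4.4.1.2); significance level 0.05 (5.6.1), taken as two-sided. Assumed: baseline-to-post correlation ρ, effect size, stratum effect, and that the MDC is at the 95% level.

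**1. The plan's own figure.** 30 / (1 − 10/100) = 33.3, rounded up to 34. This reproduces. No effect size or power enters it, so a change of analysis leaves N alone.

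**2. Following the FGA through section 5.6.1.**

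| Needed for sizing the later trial | Specified for the FGA |
|---|---|
| Mean difference between groups | Mann-Whitney statistic and p-value on change |
| SD | Median with range or interquartile range |

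Cohen's d would need a mean difference and an SD, but no rule is given for outcomes analysed by ranks.

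**3. Variance.** With equal SD σ at both times, Var(change) = 2σ²(1 − ρ) and Var(ANCOVA) = σ²(1 − ρ²), so the ratio is (1 + ρ)/2.

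| ρ | Change, in σ² | ANCOVA, in σ² | Ratio |
|---|---|---|---|
| 0.5 | 1.00 | 0.75 | 0.75 |
| 0.7 | 0.60 | 0.51 | 0.85 |
| 0.86 | 0.28 | 0.26 | 0.93 |

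**4. Power by simulation, 15 per arm.** Assumed effect 0.8 SD and stratum effect 0.3 SD. Ranges cover independent runs of the same setup.

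| ρ | Mann-Whitney on change | ANCOVA with baseline and stratum |
|---|---|---|
| 0.4 | 44-45% | 61-63% |
| 0.6 | 59-61% | 71-74% |
| 0.86 | 96-97% | 98% |

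A second simulation used the FGA scale, with scores rounded and capped at 0-30. The illustrative SD comes from the Protocol's figures: SEM = 4 / (1.96 × √2) = 1.44, and SD = 1.44 / √(1 − 0.86) = 3.86 points. For an assumed 3-point difference and no stratum effect, power was 48% against 63% (ρ 0.5), 72% against 81% (ρ 0.7) and 95% against 97% (ρ 0.86).

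**5. Type I error in the second simulation.** With an assumed 2-point stratum effect, the Mann-Whitney test rejected a true null in 0.038, 0.040 and 0.026 of runs at ρ 0.5, 0.7 and 0.86. Leaving out the stratum makes the test conservative. ANCOVA stayed between 0.046 and 0.054 across all null scenarios, despite rounding and capping.

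**6. Consequence for a later trial.** For 80% power, SD 3.86 and an assumed 2-point difference, n per arm for change against ANCOVA is 59 against 44 (ρ 0.5), 36 against 30 (ρ 0.7) and 17 against 16 (ρ 0.86).

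**7. Stability of the pilot inputs.** SE(d) ≈ √(2/15) = 0.365, so the 95% half-width is 1.96 × 0.365 = 0.72. The 95% CI of a pooled SD on 28 df runs from 0.79 to 1.35 times the estimate. The SD is usable if its uncertainty is carried forward; the observed effect is too noisy to serve as a target.

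**The case against.** The rank test has a fair defence. The FGA is a bounded ordinal score, groups are small, and the analysis is labelled preliminary. Mann-Whitney on change is valid under randomisation, and step 5 shows no inflation of type I error. All of that stands: the loss is one of efficiency. The gain from ANCOVA also rests on an assumed ρ, and at the Protocol's only FGA correlation, 0.86, it nearly vanishes. That figure is a test-retest value, and the correlation across four weeks of training may be lower, but the Protocol does not give it.

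A reader might infer several stronger things that the document does not support.

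- That baseline is ignored. The change score subtracts it; what is missing is covariate adjustment.
- That no mean difference or SD will exist for the FGA. Section 5.6.1 promises mean differences (SD) and Cohen's d in general terms, and the raw data would allow both. The defect is an unreconciled specification.
- That the pilot exists chiefly to size the next trial. Section 2.3 lists effects, feasibility and eye-movement change as objectives; sample-size input is a further purpose stated in section 5.6.1.
- That a time effect alone will trigger the pairwise tests. The wording does not say which effect counts.
- That the observed effect will be the later trial's target. This is a plausible reading of section 5.6.1, but it is not explicit.

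The point also concerns only one of two primary endpoints. Eye movements during FGA items are classed as metric and reported with means.

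**Conclusion.** The point holds as a matter of efficiency and internal consistency. The FGA comparison is valid but does not use baseline FGA as a covariate or the stratum chosen as predictive, and the outputs specified for the FGA do not match the sample-size input named in the same section. ANCOVA reduces variance by 25% at ρ 0.5, 15% at 0.7 and 7% at 0.86. The power gain for an assumed 0.8 SD effect is roughly 10 to 15 percentage points at ρ 0.6 and 1 to 2 points at ρ 0.86. ANCOVA was ahead in every scenario with a true effect, but the size of the gain depends on assumed values of ρ, effect and stratum effect. The change is worth making because it costs almost nothing; the trial's validity does not depend on it.

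**What to change.** In section 5.6.1 and the synopsis:

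1. Analyse post-intervention FGA by ANCOVA on group, baseline FGA and H&Y stratum (1-2 against 3). Report the adjusted mean difference with 95% CI, the SD and the baseline-to-post correlation.
2. Keep a stratified rank test (van Elteren) as sensitivity analysis, and keep the median as a descriptive summary.
3. Use the same ANCOVA for the metric outcomes measured at baseline and post-intervention, in place of the 2 x 2 ANOVA and its conditional pairwise tests. This removes the group test at baseline and the unclear trigger.
4. For the later trial, take the SD with its uncertainty and the correlation from the pilot, and justify the target difference separately from the observed pilot effect. An upper 80% confidence limit for the SD is one option: 1.14 times the estimate at 28 df.
5. Do not use the MDC of 4 points as that target. It is a measurement-error threshold for an individual. With SD 3.86 × 1.14 = 4.40 and ρ 0.6, n per arm = 2 × (1.96 + 0.84)² × 4.40² × 0.64 / 16 ≈ 12.1, so 13, and fewer at higher ρ. The larger trial would then be smaller than this pilot.

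The cost is wording, two degrees of freedom, and treating the 0-30 score as approximately interval. No new data are needed, and N stays 34.

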#### **4.4.1.2 Psychometric criteria**

The MDC is 4 points (Petersen et al., 2017). For individuals with Idiopathic Parkinson's Syndrome, the cut-off value is  $\leq 18/30$  points for identifying an increased risk of falls. The sensitivity is 80.6% and the specificity 80.0%. (Yang et al., 2014). The inter-rater reliability (ICC=0.99; 95% CI = 0.99-1.00) and intra-rater reliability (ICC=0.99; 95% CI = 0.99-1.00) are both excellent (Yang et al., 2016). Test-retest reliability is also very good with an ICC value of 0.86 (Petersen et al., 2017). Cronbach's alpha is 0.94, indicating excellent construct validity. (Yang et al., 2016).

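### The FGA comparison adjusts for neither baseline FGA nor the H&Y stratum, and does not supply the mean difference, SD and interval needed to size the next trial

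*Protocol*

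**What the plan says.** The synopsis lists the first primary endpoint as "1.1 Dynamic balance measured by the Functional Gait Assessment (FGA"), measured at baseline and post-intervention. Section 5.6.1 places FGA among the ordinal variables: "Ordinal scaled variables (MMSE, UPDRS, H & Y, FGA, BBS, PDQ-39, FOGQ, FES-I, BDI-II) are expressed as median (minimum, maximum or interquartile range"). Means with a confidence interval or SD are kept for metric variables.

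For ordinal data, section 5.6.1 and the synopsis give the same two steps: "New variables are generated from the difference between the post-intervention and baseline data", and then "The difference between group 1 and 2 is determined using the Mann Whitney-U test". Neither place mentions a covariate or a stratum term. The only other use of baseline values in the comparison of arms is a significance test for baseline differences.

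Section 4.1.3 stratifies the randomisation by H&Y (stages 1 and 2 versus 3): "Stratification will be based on only one relevant predictive factor for change in dynamic mobility, namely degree of disability".

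Section 5.6.1 also says what the inferential results are for. They are to feed a sample size calculation for a later trial with "sufficient power of at least 80% (based on mean differences (SD) between groups) will be performed". It closes with "The effect size is given by partial Eta squared and standardised effect size (Cohen's d"). Confidence intervals are stated for the descriptive means of metric variables and for the feasibility rates, not for a difference between arms on FGA.

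**The concern.** Two things do not fit together.

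First, the protocol names H&Y as the predictor of change in dynamic mobility and balances the arms on it, then analyses that change without it. Baseline FGA is collected and enters only by subtraction. With about 15 analysed patients per arm, information already paid for is not used.

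Second, the pilot is meant to inform the size of a larger trial. For FGA, the planned outputs are medians with range or interquartile range and a Mann-Whitney p-value. A mean difference with its SD does not come from these, and neither effect-size measure is an output of a Mann-Whitney test. What is at stake is how precise and usable the FGA result will be. The validity of the test is not in question.

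**Working it through.** **Sample size.** Section 4.1.2.3 inflates 30 for 10% failure: 30/(1 − 0.10) = 33.3, rounded up to 34. The stated figure reproduces. Thirty analysed patients at 1:1 give 15 per arm.

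**FGA spread.** Section 4.4.1.2 gives an MDC of 4 points and states: "Test-retest reliability is also very good with an ICC value of 0.86". Taking the MDC as a 95% MDC (assumed):

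- SEM = 4/(1.96 × √2) = 1.44
- SD = 1.443/√(1 − 0.86) = 3.86

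**Variance of the difference between arms**, with n per arm and baseline-post correlation ρ:

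- change score: 2·SD²·(1 − ρ)·(2/n)
- baseline-adjusted: SD²·(1 − ρ²)·(2/n)
- ratio: (1 + ρ)/2

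The only correlation in the protocol is the test-retest ICC of 0.86. The correlation across four weeks of training is not given, so 0.7 and 0.5 are assumed as a range. The 95% half-widths use 15 per arm and t quantiles on 28 df (change) and 26 df (model with baseline and stratum). They take no credit for any variance explained by H&Y.

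| ρ | variance ratio | half-width, change | half-width, adjusted |
|---|---|---|---|
| 0.86 | 0.93 | 1.53 | 1.48 |
| 0.7 | 0.85 | 2.23 | 2.07 |
| 0.5 | 0.75 | 2.88 | 2.51 |

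**Chance baseline imbalance.** One standard error of the baseline difference is 3.86 × √(2/15) = 1.41 points. It shifts the change-score contrast by (1 − ρ) × 1.41, that is 0.20, 0.42 and 0.70 points at ρ = 0.86, 0.7 and 0.5.

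**Power by simulation.** Assumptions: 15 per arm, true effect 2.5 points, baseline mean 21, common gain 2 points, scores rounded and capped at 30, no stratum effect, two-sided 5% level.

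| ρ | Mann-Whitney on change | t-test on change | ANCOVA | total gain |
|---|---|---|---|---|
| 0.86 | 81% | 84% | 87% | 6 points |
| 0.7 | 52% | 56% | 64% | 12 points |
| 0.5 | 34% | 37% | 47% | 13 points |

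The step from the first to the second column is the effect of ranks versus a parametric test on normally generated data, roughly 2 to 4 points. The remainder is baseline adjustment. Repeat runs agreed to within about 2 points, and type I error was 4–5% for both the planned test and ANCOVA.

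A second simulation used an assumed 3-point effect, baseline mean 22, a 20:10 stratum split and an assumed stratum effect of 4 points, with 0 or 2 further points on change. Power was about 44–45%, 63–66% and 90–91% for Mann-Whitney against 63%, 78% and 96% for ANCOVA with baseline and stratum, at ρ = 0.5, 0.7 and 0.86. Type I error of the planned test was 3–5%. This run does not separate the H&Y contribution from that of baseline, so the H&Y gain remains unquantified.

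**The case against.** Three stronger readings are tempting, and the protocol supports none of them.

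- **That baseline is ignored.** The change score subtracts each patient's own baseline and is unbiased over randomisation. What is missing is adjustment. The shift from imbalance is conditional on a chance difference, and at ρ = 0.86 it is only 0.2 points per standard error.
- **That the test is invalid.** Simulated type I error was about 3–5%. Leaving out the stratum does not inflate it.
- **That no effect measure is foreseen.** Section 5.6.1 does name mean differences with SD, Cohen's d and partial eta squared. The accurate complaint is that the analysis fixed for FGA does not produce them and that no interval is attached.

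Other objections carry weight. This is a pilot sized by rules of thumb, its inference is described as preliminary, and power on FGA is not a design claim. At the one documented correlation the precision gain is small. The 2.5-point effect is assumed and lies below the MDC of 4. At an assumed 4-point effect, power is 99% against nearly 100% at ρ = 0.86, though the gap reopens at 0.7 (89% against 96%) and 0.5 (70% against 86%).

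An analysis plan not shown here could add an interval or a supporting adjusted model, so the missing interval alone would be weak ground. The choice of test, however, is fixed in the protocol. Finally, ANCOVA on a capped 0–30 score departs from the protocol's ordinal classification. That choice is debatable, which is why a rank-based analysis should stay.

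**Conclusion.** The point holds as a minor to moderate improvement that costs nothing in data. The planned FGA test is valid but adjusts for neither baseline nor the stratum that the protocol itself calls predictive. The FGA outputs also do not match the quantities section 5.6.1 wants for planning the next trial. That mismatch, and the unused stratum, stand whatever the correlation.

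The precision loss does depend on the correlation: a 7% variance reduction forgone at 0.86, 15% at 0.7 and 25% at 0.5. This corresponds to about 6 to 13 points of power for an assumed 2.5-point effect, part of it due to ranks rather than adjustment. These figures rest on an SD derived from the MDC and ICC, 15 analysed patients per arm, approximately normal scores and an assumed range for the four-week correlation.

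**What to change.** In section 5.6.1 and the synopsis, make the FGA analysis an ANCOVA of the post-intervention score on arm, baseline FGA and H&Y stratum (1–2 versus 3). Report the adjusted mean difference with its 95% confidence interval and the residual SD, and state that these are the figures to be used for sizing the next trial.

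Keep a rank-based analysis as a check that respects the ordinal classification: either rank ANCOVA with the same covariates, or a van Elteren test stratified by H&Y.

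The cost is wording in two places. Both covariates are already collected, and no further patients, visits or measurements are needed.

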## 2.4 Null hypotheses

**Primary null hypothesis:** There is no difference between the effects of an everyday physiotherapy training programme with eye movement training and such a training programme without eye movement training on dynamic balance in people with idiopathic Parkinson's syndrome.

**Secondary null hypotheses:** There is no difference between the effects of an everyday physiotherapy training programme with gaze movement training and such a training programme without gaze movement training on functional mobility with and without manual multi-task, static balance, walking speed, health-related quality of life, freezing of gait, fall-associated self-efficacy, depression, fall rate and eye movements during dynamic balance tasks and specific training items in individuals with Idiopathic Parkinson's Syndrome.

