#### **4.1.2.3 Number of participants and sample size**

For this study, 34 people with Idiopathic Parkinson's Syndrome will be included. Of the 34 people with Parkinson's disease, 17 will be randomised to intervention group 1 and 17 to control group 2.

According to Julious, participants per group are considered a minimum sample size for a pilot study. (Julious, 2005) while Browne specifies a number of participants of 30 for a two-arm study. (Browne, 1995). Therefore, to evaluate the feasibility criteria and preclinical effects of the experimental intervention compared to the conventional control intervention, a sample size of 34 is aimed for, based on 30 participants, including an expected failure rate of 10% and using the formula  $N = n / (1 - (z/100))$ . Here, n is the number of participants (30) and z is the expected failure rate (10%).

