### 4.3.2 Data collection and investigators

The data collection will be carried out by trained and blinded raters (doctors, physiotherapists) at baseline, post-intervention and at the follow-up call. After the end of the intervention, the participants' experience and acceptance of the intervention will be assessed in focus groups. A follow-up call will take place one month after the end of the intervention, i.e. two months after the baseline assessment. This survey will include a very short interview, the fall rate during the 4-week intervention period and two questionnaires (FOGQ, FES-I).

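### The Kruskal-Wallis test pooling groups and visits for FES-I and FOGQ does not test the difference between arms, and no other test is named for their follow-up values

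*Protocol*

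**What the plan says.** Protocol section 5.6.1 gives FES-I and FOGQ a rule of their own because they have a third measurement. The rule is that "a Kruskal Wallis test is performed across all groups and test time points". The synopsis repeats the sentence under Statistical analysis, so it is not a slip in one place.

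The scores come from the same patients. Table 2 (section 4.3.3) marks both scales at baseline, post-intervention and follow-up, and section 4.3.2 says the call includes "two questionnaires (FOGQ, FES-I").

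The secondary null hypothesis in section 2.4, which lists freezing of gait and fall-associated self-efficacy among its outcomes, is a statement about arms: "There is no difference between the effects of an everyday physiotherapy training programme with gaze movement training and such a training programme without" it.

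Elsewhere section 5.6.1 respects the pairing. Ordinal outcomes are compared between arms by Mann-Whitney U on post-intervention minus baseline, and metric outcomes by an ANOVA with time as a within-factor.

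**The concern.** Kruskal-Wallis is a test for independent samples, and its null is that every sample comes from the same distribution. Applied across groups and visits, it treats repeated scores from one patient as unrelated, and it mixes three questions: do scores change over time, do the arms differ, and does the change differ by arm. Only the last is the hypothesis of section 2.4.

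A change over time in both arms is plausible. Section 1.3 says both groups receive the training programme to the same extent on top of inpatient rehabilitation, and section 4.2.1 gives every participant eight 30-minute physiotherapy sessions a week. Section 5.6.1 wants the inferential analysis to show trends in effectiveness. A p-value driven by rehabilitation common to both arms could be misread as such a trend in favour of gaze training.

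**Working it through.** **1. What the test compares.** 2 groups × 3 visits = 6 cells, so 6 − 1 = 5 degrees of freedom. With 34 patients there are 34 × 3 = 102 scores from 34 independent units.

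**2. Sample size.** Section 4.1.2.3 is "based on 30 participants, including an expected failure rate of 10" per cent. Its formula gives 30 / (1 − 10/100) = 33.3, rounded up to 34, which reproduces the stated figure; "17 will be randomised to intervention group 1 and 17 to control group 2". The check therefore uses 17 per arm (all randomised) and 15 per arm (after the expected losses).

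**3. The two nulls.** Let F(g,t) be the score distribution in arm g at visit t.

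- Kruskal-Wallis: F(1,1) = F(1,2) = F(1,3) = F(2,1) = F(2,2) = F(2,3).
- Section 2.4, in change form: the distribution of change from baseline is the same in arms 1 and 2.

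If both arms shift by the same amount after baseline, the first null is false and the second is true. The same holds if the arms differ by a constant already present at baseline.

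**4. Size.** The protocol gives no SD, correlation or expected change for these scales. Assumed: mean 30, SD 9, exchangeable within-patient correlation, scores rounded and clipped to 16–64 (16 items scored 1–4, section 4.4.11.1), two-sided 5% level, 4,000 simulated trials per setting. Monte Carlo standard error: √(0.25 × 0.75 / 4000) = 0.7 points at 25%, and √(0.05 × 0.95 / 4000) = 0.3 points at 5%.

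Kruskal-Wallis rejection with equal improvement in both arms, 17 per arm:

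| Correlation | 0 SD | 0.3 SD | 0.5 SD | 0.8 SD | 1.0 SD |
|---|---|---|---|---|---|
| 0.5 | 3.9% | 9.5% | 29.5% | 83.4% | 97.0% |
| 0.7 | 3.9% | 8.6% | 24.9% | 84.2% | 98.6% |
| 0.8 | 5.0% | 8.0% | 23.0% | 85.4% | 98.9% |
| 0.9 | 5.1% | 8.2% | 22.0% | 87.0% | 99.6% |

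Mann-Whitney on change from baseline, in the same settings and at either later visit, rejects in 3.9–5.6%. With 15 per arm and correlations 0.5 to 0.9, Kruskal-Wallis rejects in 18–24% at 0.5 SD and 74–76% at 0.8 SD.

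A constant 0.5 SD difference present from baseline, with no change in either arm, gives 30–34% (17 per arm).

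**5. When only the gaze arm improves (17 per arm).**

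| Correlation | 0.5 SD: Kruskal-Wallis | 0.5 SD: Mann-Whitney on change | 0.8 SD: Kruskal-Wallis | 0.8 SD: Mann-Whitney on change |
|---|---|---|---|---|
| 0.5 | 29.2% | 25.0% | 72.7% | 52.8% |
| 0.7 | 26.2% | 38.4% | 68.7% | 73.5% |
| 0.8 | 25.2% | 54.4% | 65.8% | 87.6% |
| 0.9 | 24.4% | 80.1% | 64.8% | 98.9% |

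Comparing the 0.5 SD columns of the two tables, Kruskal-Wallis rejects about equally often when gaze training adds nothing and both arms improve (22–30%) as when the gaze arm alone improves (24–29%). Its p-value cannot separate the two cases.

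**The case against.** **A between-arm test may already exist at post-intervention.** Section 5.6.1 first sets Mann-Whitney on change for ordinal data and lists FOGQ and FES-I as ordinal. The Kruskal-Wallis sentence does not say that it replaces that rule. This stands as a reasonable reading. It limits the defect but does not remove it, because the general rule covers only post-intervention minus baseline. For follow-up, Kruskal-Wallis is the only test named.

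**One test per visit may have been meant.** The text speaks of a single test across groups and time points, so this is not what it says. If it was intended, the sentence still needs rewriting.

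**The false-rejection rate depends on an unstated shift.** This stands. At 0.3 SD it is only 7–10%, and the protocol forecasts no change on either scale.

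**A reader might infer that ignoring the repeated measurements inflates the error rate by itself.** The check does not show that. With neither a time nor a group effect, rejection is about 3–5%. The harm comes from the null being tested.

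**A reader might infer that the test always dilutes a real effect.** It does not. At correlation 0.5 it rejects as often as Mann-Whitney on change or more often. The loss appears only from about 0.7 upwards, and at 0.7 it is small for a 0.8 SD effect (68.7% against 73.5%). The protocol gives no correlation to settle the matter.

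**The weight is limited.** These are two of many secondary endpoints in a 34-patient pilot whose inference is called preliminary. The primary FGA score falls under Mann-Whitney on change, no feasibility criterion in section 4.4.14.1 uses either scale, and the later sample size is to rest on mean differences and SDs. All of this stands and lowers the severity.

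**Conclusion.** The rule is wrong as written and should be fixed. A significant Kruskal-Wallis result would not address section 2.4, since equal improvement in both arms, or a baseline imbalance, can produce it. With 15 to 17 per arm and correlation 0.5 to 0.85, equal improvement gives about 7–10% rejection at 0.3 SD, 20–30% at 0.5 SD and 75–87% at 0.8 SD, against about 3–6% for Mann-Whitney on change. These figures rest on the assumed distribution, correlation and shifts; the mismatch between the two nulls does not.

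If the general ordinal rule also applies at post-intervention, the defect is confined to the follow-up values, for which no valid between-arm test is named. A reader might infer that the trial's only evidence on durability is lost. The documents do not support that: section 4.4.13 and Table 2 also collect falls at the follow-up call. FES-I and FOGQ are the only questionnaire scales collected then. Medians by arm and visit would also remain interpretable.

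**What to change.** In section 5.6.1 and the synopsis, replace the Kruskal-Wallis sentence by extending the protocol's own rule: for FES-I and FOGQ, compare the arms by Mann-Whitney U on post-intervention minus baseline and, separately, on follow-up minus baseline, and report the between-arm difference with a 95% CI at each visit. The comparison may be stratified by the Hoehn & Yahr stratum used in randomisation (section 4.1.3).

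A repeated-measures model with a group-by-visit term is an alternative, but on raw scores it departs from the protocol's ordinal treatment of these scales, so the rank-based version is the smaller change.

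The cost is one sentence in two places. No visit, measurement or patient is added, and the unstratified test is already planned for the other ordinal outcomes.
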